### Measurements

#### **
*Clinical data*
**

A questionnaire for data collection was developed. This included assessment of socio-demographic data, weight, height, waist, hip and neck circumferences, healthy behaviors, daily exercise routines, smoking history, consumption of alcohol or other toxic habits, previous medical diagnosis, presence of comorbidities, personal and family history of disease, and medication use. Daytime somnolence is assessed with the Epworth test [19]. Blood pressure is measured according to international guidelines by certified nurses blinded to the presence or absence of OSA [20]. Spirometry is performed according to the standard criteria [21].

#### **
*Sleep study*
**

At our clinic, full polysomnography is used for patients believed to suffer from sleep disorders other than or in addition to sleep apnea, which are not to be included in the present study. For the rest of the patients with suspected OSA diagnosis, a type 3 portable sleep monitor will be used. The sleep study includes continuous recording of airflow from a nasal pressure cannula, thoracic-abdominal motion, oxygen saturation, snoring and body position. Results from all sleep studies are analyze using standard criteria by trained personnel that are blind to the present protocol. An apnea is defined as an absence of airflow of 10 seconds or longer; a hypopnea as an airflow reduction (>50%) lasting ≥ 10 seconds with a decrease in oxygen saturation over 4%. Obstructive apneas are defined as the absence of airflow in the presence of thoracic-abdominal motion. The AHI is calculated based on the average number of apnea plus hypopnea episodes per hour of recording time. Optimal titration of CPAP is obtained by using auto-CPAP (Autoset-T; ResMed, Sydney, Australia), according to previous validation procedures by the Spanish Sleep and Breathing Group [22]. Compliance with CPAP will be measured using the machines’ internal timers. All patients will attend a new sleep study every year.

#### **
*Laboratory analysis*
**

At baseline and every year, whole blood samples are drawn using a 21G butterfly needle into serum gel, EDTA, sodium fluoride and PaxgeneW tubes (PreAnalytix GmbH, Switzerland). Serum glucose, triglycerides, total cholesterol and HDL cholesterol will be measured by spectrophotometry (Chemical Analyzer ILAB 650, Instrumentation Laboratory), and serum apolipoproteins A and B, will be measured by kinetic nephelometry (Immunochemistry Analyzer IMMAGE 800, BeckmanCoulter). Within two hours after collection, high sensitive C-reactive protein (CRP) will be measured based on a particle-enhanced turbidimetric immunoassay technique. For biobanking, about 15 ml of EDTA blood and 5 ml of blood without anticoagulant for serum preparation are to be fractionated into plasma, serum and whole blood and in 1 ml dot-coded metal-free cryotubes are to be stored at -80°C. Inflammatory markers to be assessed are shown in Table 2.

**Table 2 T2:** Outcome measurements in the Epigenetics in Obstructive Sleep Apnea (EPIOSA) study

**Measurement**	**Description**	**Frequency of assessment**
Questionnaires, Dietary, Epworth Sleepiness Scale		Each visit
Vital signs	Including sitting blood pressure, heart rate, height and weight	Each visit
Exhaled carbon monoxide	Confirmation of smoking status	Each visit
Spirometry	Post-bronchodilator FVC, FEV1 and FEV1/FVC	Baseline
Electrocardiogram	12-lead resting electrocardiogram	Baseline
Sleep Study	At home type 3 monitor for diagnosis and at home autoCPAP for CPAP titration (if appropriated)	Baseline and every year
Blood sample	Standard biochemistry and lipid markers: Total cholesterol, LDL, HDL, TG, Apo A, Apo B.	Baseline and last visit
	Inflammatory markers: TNF-α, IFN-ϒ, IL-1β, IL-6, IL-8, IL-10.	
Urine sample	Microalbuminuria, 8-isoprostane	Baseline and every year
Carotid Ultrasonography	High-resolution B-mode assessment of carotid artery intima-media thickness and plaque	Baseline and every year
Magnetic resonance imaging	Cerebral microbleeds detection	Baseline and last visit
Flow cytometry	Fresh peripheral blood T-cell phenotype	Baseline and last visit
DNA methylation	Genome-wide DNA methylation status	Baseline and last visit
miRNA microarray analysis	Levels of candidate miRNAs regulated by aberrant DNA methylation	Baseline and last visit

#### **
*Flow cytometry*
**

At baseline, whole fresh blood with EDTA will be obtained for flow cytometry. Table 3 shows the cells stained, and also the antibodies and kits used. The samples will be incubated for 15 min at room temperature, then acquired in a GALLIOS flow cytometer (Beckman Coulter) and analyzed with the KALUZA software (Beckman Coulter).

**Table 3 T3:** Subset of T cell population to be analyzed

**Antibody-kit**	**Clone**	**Fluorescence**	**Catalog number**
CD4-CD8- CD3	CD4:HP2/6, CD8: 143–44, CD3: 33-2A3	CD4: FITC CD8: PE CD3: PERCP	4FI8PEI3PPI-50 T. IMMUNOSTEP
CD11c	BU-15	FITC	11CF3-100 T IMMUNOSTEP
CD14	47-3D6	APC	14A-100 T IMMUNOSTEP
CD15	MCS-1	FITC	15 F-100 T IMMUNOSTEP
CD16	3G8	PE	16PE2-100 T IMMUNOSTEP
CD45	HL30	CF BLUE	45CFB2-100 T IMMUNOSTEP
CD45 RA	HI100	APC	45RAA2-100 T IMMUNOSTEP
CD 62 L	DREG 56	APC-eFluor 780	47-0629 eBioscience
Human regulatory T cell cocktail*	CD4: SK3, CD25: 2A3, CD127: HIL-7R-M21	CD4: fitc, CD 25: PE-Cy7, CD127: Alexa fluor 647	560249 (BD Pharmigen)

*T reg was defined as CD4+/CD25+/CD127 (low/-) phenotype (ref. [23]).

#### **
*DNA methylation analysis*
**

Part of the blood samples collected in EDTA tubes are stored at -80°C until DNA isolation, which is performed in the Department of Molecular Biology at the Faculty of Veterinary of the University of Zaragoza. Genomic DNA is obtained with the use of the illustra blood genomic Prep Midi Flow Kit (GE Healthcare, UK) following the manufacturer’s instructions. Genome-wide DNA methylation profiles will be studied in approximately 1 μg of genomic DNA treated with sodium bisulfite. The converted DNA will be analyzed using Illumina’s Infinium Human Methylation 450 BeadChip assay (Illumina, San Diego, CA, USA). To minimize position effects, cases and controls will be randomly distributed. The assay allows determination of DNA methylation levels at >450,000 CpG sites covering all designable RefSeq genes, including promoter, 5′, and 3′ regions. It captures CpG islands and shores, non-CpG methylated sites, microRNA promoter regions and disease-associated regions identified through genome-wide association studies [24]. Illumina array data will be processed using the Methylation Module of GenomeStudio v1.9 software. To identify differentially methylated regions (DMRs), we will use a 1-kb sliding window and apply Fisher’s method to combine P values for each 1-kb region on the basis of all probes within each window [25]. Significant DMRs will be selected at a 1% FDR on autosomes and 5% FDR on chrX. After statistical analyses, the methylation patterns of the gene of interest will be confirmed by sequencing of the 24 bisulfite-treated DNA samples used for the genome wide analysis.

#### **
*Gene expression analysis*
**

Blood samples stored at -80°C in PaxGene (TM) tubes will be used for total RNA isolation using PAXgene Blood RNA Kit (Qiagen, Venlo, Netherlands). Quantitative real time polymerase chain reactions (qRT-PCR) will be performed to test whether differential methylation patterns of the selected genes affect their expression level. Complementary DNA will be synthesized from total RNA using random hexamers and the SuperScript^®^ III First Strand Synthesis Kit (Life Technologies, Carlsbad, California, US). Primers and TaqMan^®^ probes will be selected from the Applied Biosystems Inventories Assays and qRT-PCR will be performed in a The StepOne™ Real-Time PCR System (Applied Biosystems, Life Technologies, Carlsbad, California, US).

#### **
*MicroRNA analysis*
**

This study is based in the expression of 96 miRNAs. These miRNAs have been carefully selected based on those predicted by bioinformatic algorithms and databases to regulate genes known to be relevant to inflammation. Total RNA will be extracted from cryopreserved samples using Paxgene Blood miRNA kit (PreAnalitiX) according to the manufacturer’s protocol. RNA integrity will be tested using the 2100 Bioanalyzer (Agilent Technologies, Santa Clara, California, US). Samples will be reverse transcribed using the Taqman^®^MicroRNA Reverse Transcription Kit (Applied Biosystems, Life Technologies, Carlsbad, California, US) and mature miRNAs will be quantified by real-time PCR using the Taqman^®^MicroRNA Assays [26]. miRNA expression will be analyzed using the BioMark 96:96 Dynamic Array (Fluidigm Corporation, San Francisco, California, US). Data will be analyzed using the BioMark Real-Time PCR Analysis Software v2.0 (Fluidigm). The Ct value will be used for analysis by the 2^-∆∆Ct^ method [27].

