### Statistical analyses

Groupwise comparisons (n >2) will be performed using a nonparametric Kruskal-Wallis test followed by a Mann–Whitney U test as appropriate. Pairwise comparisons were performed using a nonparametric Mann–Whitney test unless otherwise indicated. Chi square tests will be performed for categorical variables. Regression models will be applied to assess the effect of OSA, biomarkers, peripheral lymphocytes and epigenetic changes on CIMT, carotid plaque and cerebral microbleeds. All models will be adjusted for age and BMI, and additionally for covariables that may change the estimated risk beyond 5% Specific statistics procedures will be performed for the arrays as described above. STATA-12 for Windows (STATA CORP, TX, USA) are to be used for all analyses.

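### Combining neighbouring-probe P values by Fisher's method, with no stated allowance for their correlation, leaves the 1% and 5% FDR for methylated regions unassured as written

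*Protocol article*

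**What the plan says.** The method is given in the protocol article under Measurements, DNA methylation analysis.

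- **Array:** "The assay allows determination of DNA methylation levels at >450,000 CpG sites".
- **Window:** "To identify differentially methylated regions (DMRs), we will use a 1-kb sliding window".
- **Combination rule:** Fisher's "method to combine P values for each 1-kb region on the basis of all probes within each window", with a citation for the method.
- **Selection:** "Significant DMRs will be selected at a 1% FDR on autosomes and 5% FDR on chrX". The procedure that yields the FDR is not named.
- **Follow-up:** "the methylation patterns of the gene of interest will be confirmed by sequencing", done on "sequencing of the 24 bisulfite-treated DNA samples used for the genome wide analysis". Expression of the selected genes is then tested by qRT-PCR.

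The Statistical analyses section adds nothing on this point and refers back: "Specific statistics procedures will be performed for the arrays as described above". The article mentions no adjustment for between-probe correlation, no permutation and no empirical null. It gives neither the number of probes per window nor the correlation between them.

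**The concern.** Fisher's statistic follows a chi-square distribution on 2k degrees of freedom only if the k combined P values are independent. A 1-kb window groups adjacent CpG probes read in the same subjects, the setting in which independence is least plausible. Dependence leaves the mean of the statistic unchanged but widens its distribution. The excess is greatest in the far tail, where FDR selection works, and it grows with the number of probes, so probe-dense windows are favoured.

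At stake is the list of regions from which genes go forward to sequencing and expression work. Sequencing the same 24 samples checks the measurement. It cannot show whether a group difference in those 24 people arose by chance. The FDR threshold is therefore the only stated guard against chance in the selected list.

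**Working it through.** **Inputs from the article:** Fisher's method over all probes in a 1-kb window; FDR 1% (autosomes) and 5% (chrX); 24 samples in the genome-wide analysis.

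**Assumptions, not in the article:** k = 2, 3, 5 or 10 probes per window; equal correlation ρ between the probes' z scores; two-sided P values; for FDR, Benjamini-Hochberg at 1% on 100,000 non-overlapping windows, of which 1% or 5% truly differ by 3 standard errors at every probe.

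**Step 1. Statistic.** T = −2 Σ ln(pᵢ), referred to chi-square on 2k df. Under independence Var(T) = 4k. With equal correlation, Var(T)/4k = 1 + (k − 1)c, where c is the correlation between two probes' values of −2 ln p. In simulation c is close to ρ². For k = 5 and ρ = 0.5 this gives 1 + 4 × 0.25 = 2.00 (simulated 1.98). For k = 5 and ρ = 0.2 it gives 1 + 4 × 0.04 = 1.16 (simulated 1.15 to 1.16). Because c behaves like ρ², weak negative correlation also inflates slightly: at ρ = −0.1 the realised FDR was 1.3% to 1.9%.

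**Step 2. The plan's own figure.** The 1% is a chosen threshold, so there is nothing to derive. At ρ = 0 the procedure delivers it: realised FDR 0.8% to 1.1%, with null rejection at about the nominal rate.

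**Step 3. Null rejection at nominal P<0.0001, as a multiple of nominal** (at least 1,000,000 null windows per setting):

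| Probes k | ρ = 0.2 | ρ = 0.5 | ρ = 0.7 |
|---|---|---|---|
| 3 | 3 | 19 | 43 |
| 5 | 7 | 65 | 138 |
| 10 | 24 | 219 | 421 |

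At ρ = 0.4 the multiples are about 12 (k = 3) and 36 to 37 (k = 5). The mildest correlated case tried at this step, k = 2 and ρ = 0.2, gives about 2.

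**Step 4. Realised FDR at nominal 1%, when 1% / 5% of windows truly differ:**

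| Probes k | ρ = 0.2 | ρ = 0.5 | ρ = 0.7 |
|---|---|---|---|
| 3 | 3% / 2% | 21% / 10% | 40% / 18% |
| 5 | 7% / 4% | 47% / 21% | 69% / 36% |
| 10 | 20% / 9% | 76% / 43% | 87% / 57% |

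One cell by hand (k = 5, ρ = 0.5, 1% true): about 1,638 windows are called, so the P cut-off is 0.01 × 1,638 / 100,000 = 0.000164. Valid P values would give 99,000 × 0.000164 ≈ 16 false calls, and 16 / 1,638 ≈ 1%. The simulated false share is 0.467, or 0.467 × 1,638 ≈ 765 false calls. With no true region at all, the same k and ρ still yield about 460 calls in 100,000.

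**Step 5. Alternatives** (1% true, ρ = 0.2 to 0.7). Referring the same statistic to a null that keeps the between-probe correlation gives a realised FDR of 0.5% to 1.4%. A Brown-type scaled chi-square leaves 2.4% to 11.3%: it matches the variance but not the far tail.

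**Limits.** The simulations ignore the overlap of sliding windows and the discreteness of tests on 24 samples. The 5% chrX threshold was not simulated; the direction is the same.

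**The case against.** A reader might infer that region P values are far too small and that the 1% FDR fails. The documents do not support that. The FDR procedure is not named, and the source cited for the window method is not at hand. If the FDR is obtained by permuting sample labels, it could hold despite the dependence. The probes per window, their correlation, the share of true regions and the effect size are all absent too. At the mild end (3 probes, correlation 0.2) the realised FDR is only 2% to 3%.

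It can also be said that a condensed article leaves such calibration to a fuller plan, and that this is a discovery screen in a non-interventional cohort. The power statement concerns IMT by CPAP treatment, and the screen is not shown to affect the regression models for CIMT, plaque or microbleeds. Aim 4 also covers cytometry and RNA work.

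Most of this stands, and it sets the wording and the priority. It does not remove the point. The article goes beyond silence: it states a combination rule and an error rate, and taken as written the first does not deliver the second when probes are correlated. The sequencing step does not answer it either.

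**Conclusion.** The point holds in a limited form. As written, Fisher's method with no allowance for correlation between neighbouring probes gives region P values that are too small wherever such correlation exists, so neither the 1% nor the 5% FDR is assured. The direction was the same in every correlated setting tried. The size rests on assumed inputs: about 2 to 421 times nominal at P<0.0001 for 2 to 10 probes, and a realised FDR of about 2% to 87% at nominal 1% for 3 to 10 probes, both over correlations of 0.2 to 0.7. There is no excess at zero correlation. This is a should-fix confined to the methylation discovery step.

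**What to change.** Keep the 1-kb window and the Fisher statistic, but calibrate it differently. Permute group labels across whole samples, so that each person's probes stay together. Recompute every window statistic, and derive the region P values, or the FDR itself, from the permuted results. Then apply the 1% and 5% thresholds and name the FDR procedure. If the cited method already does this, one sentence saying so settles the matter.

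With 24 samples the permutation P values are coarse. If the split were 12 and 12 (an assumption), there are 24!/(12! × 12!) = 2,704,156 relabellings, so the smallest two-sided P for one window is 2 / 2,704,156 ≈ 0.0000007. Estimating the FDR directly from permuted against observed counts, or pooling the null across windows with similar probe numbers, avoids leaning on that floor. A Brown-type correction is better than no correction but should not be relied on alone.

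The cost is a sentence or two and a different routine on the same array data, with no change to recruitment or sampling. Fewer regions will be declared. At 5 probes and correlation 0.5, simulated power falls from 0.89 to 0.40, although the 0.89 came with a realised FDR of about 45% to 47%.

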### Power considerations

The calculation of EPIOSA’s planned sample size of 300 patients and 50 matched controls, is based on three estimations: a) in pediatric patients, those with OSA (n = 37), showed a reduced Treg population and altered Th1:Th2 balance toward Th1 predominance compared with non-OSA controls (n = 13) [30]; b) differences among DNA methylation in inflammatory genes were observed among OSA patients with high hsCRP (n = 31), compared with normal non-OSA controls (n = 31) [16]; and C) a randomized study showed that effective treatment of OSA with continuous positive airway pressure for 4 months significantly decreases IMT as early signs of atherosclerosis in 24 patients with severe OSA [31]. We expected a loss to follow-up of an average of 2% per year. In this way at the end of the 5-year follow-up we hope to analyze outcomes in 270 patients with OSA and 45 without OSA. This sample size ensures to analyze subgroups of patients according with prescribed treatment for OSA. Specifically, the sample will have 80% power to detect average IMT differences when comparing OSA patient treated and non-treated CPAP. The power is calculated based on a 2 SD with a significance level of 0.0125.

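### Methylation hits are to be confirmed by sequencing the same 24 samples that produced them, which checks the array reading but does not replicate the finding

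*Protocol article*

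**What the plan says.** The protocol article, Measurements, DNA methylation analysis, describes array profiling of bisulfite-treated DNA: "The assay allows determination of DNA methylation levels at >450,000 CpG sites". P values of probes within 1-kb windows are combined by Fisher's method, and "Significant DMRs will be selected at a 1% FDR on autosomes and 5% FDR on chrX". The methylation pattern of the gene of interest then "will be confirmed by sequencing of the 24 bisulfite-treated DNA samples used for the genome wide analysis".

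Three other places bear on this:

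- Table 2, titled "Outcome measurements in the Epigenetics in Obstructive Sleep Apnea (EPIOSA) study", lists "Genome-wide DNA methylation status" at baseline and last visit. It has no column for the number of subjects and marks no subset.
- Statistical analyses: "Regression models will be applied to assess the effect of OSA, biomarkers, peripheral lymphocytes and epigenetic changes on CIMT", and also on carotid plaque and cerebral microbleeds. No subset is named.
- Power considerations sets the cohort at 300 patients and 50 controls and expects 270 and 45 at five years. For methylation it cites a paediatric comparison of 31 v 31.

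The number 24 appears once in connection with methylation. No group split, time point or selection rule goes with it.

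**The concern.** A difference between groups in a small sample has three possible sources: a real difference, an error of the array, or the chance make-up of the people sampled. Sequencing the same DNA can separate the second from the other two. It cannot separate the first from the third, because the same people are compared again.

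Selection adds a second problem. Regions are chosen because their observed difference is large, so the estimates in chosen regions are too large on average. Re-measurement in the same people largely repeats that excess.

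The sequenced regions decide which genes go on to the expression work, and they feed the aim of finding novel epigenetic factors linked to poor outcome. If they are reported as confirmed on this basis, the label promises more than the design delivers.

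**Working it through.** **Inputs from the article.** 24 samples, used for both array and sequencing. False discovery rate 1% on autosomes and 5% on chromosome X. Cohort 300 + 50 = 350, with 270 + 45 = 315 expected at the last visit.

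**The article's own figures.** The 24 has no stated derivation, so it cannot be reproduced. The follow-up figures can be. A 2% loss per year over 5 years gives 300 × 0.90 = 270 and 50 × 0.90 = 45. Compounded, 300 × 0.98^5 = 271.2 and 50 × 0.98^5 = 45.2.

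**1. What same-sample confirmation does to chance hits.**

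Assumptions, none of them in the article: 12 v 12 split; no true difference at any site; a t-test per site; hits taken at p<0.001; confirmation means p<0.05 in the same direction. Array and sequencing readings on one sample correlate at r. Two million null sites were simulated per value of r.

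| r | Chance hits confirmed in the same 24 samples |
|---|---|
| 0.5 | about 35% |
| 0.7 | about 67% |
| 0.8 | about 87% |
| 0.9 | about 99% |
| 0.95 | about 99.9% |

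In 24 independent samples the theoretical share is 0.05 / 2 = 2.5% (simulated 2.1% to 2.7%). A repeat run with a different random seed gave 35%, 68%, 87% and 99% for r = 0.5, 0.7, 0.8 and 0.9.

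**2. Inflation of the estimates.**

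Under the same assumed split and threshold, a hit needs |t| > 3.79 on 22 degrees of freedom. The smallest observed standardised difference that can be selected is 3.79 × √(1/12 + 1/12) = 3.79 × 0.408 = 1.55 SD. Wherever the true difference is below 1.55 SD, every selected estimate overstates it. A false discovery rate governs which regions are declared and leaves their estimates as they are.

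**3. How far 24 is from the cohort.**

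- All subjects at two visits, without loss: 350 × 2 = 700 samples. With the expected loss: 350 + 315 = 665.
- 24/700 = 3.4% and 24/665 = 3.6%.
- If each sample is a different man, 24/350 = 6.9% of subjects.

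**4. Why the number matters.**

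Difference detectable with 80% power, two-sided noncentral t, at assumed single-site levels:

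| Groups | P = 1e-5 | P = 1e-7 |
|---|---|---|
| 12 v 12 (assumed) | 2.75 SD | 3.65 SD |
| 20 v 4 (near the cohort's 6:1 ratio) | 3.69 SD | 4.90 SD |
| 31 v 31 | 1.45 SD | 1.78 SD |
| 270 v 45 | 0.86 SD | 1.02 SD |

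These figures are only a guide to scale. The plan tests combined P values over 1-kb windows and selects by false discovery rate, so it does not test single sites at these levels.

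**The case against.** **The sentence may mean only technical validation.** It speaks of methylation patterns being confirmed by sequencing and never calls this replication. That reading is open, and as an assay check the step is sound. But the article describes no other methylation check. The expression work by qRT-PCR is not stated to use other subjects. Even on the milder reading, replication is absent from the methylation plan as described.

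**Chance is already controlled.** A reader might infer that hits from so few samples must be mostly chance. The article does not support this. It sets a false discovery rate one sentence before the one at issue, and if that procedure is valid, about 1% of declared autosomal regions are expected to be false. Small numbers mainly cost power and inflate estimates. One reservation remains: Fisher's method treats the P values in a window as independent, and the article states no adjustment for correlation between neighbouring probes. The full plan may contain one.

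**Same-sample sequencing is not useless.** A reader might infer that it would reject almost no false hit. That holds only where the two assays agree closely. At r = 0.5 it would reject about 65% of chance hits, and at r = 0.7 about a third.

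**The 24 does not contradict Table 2.** A reader might infer a contradiction, or that the carotid regressions rest on 24 samples. Table 2 gives no number of subjects, whereas the imaging section says outright that carotid thickness and MRI are done in all subjects. The regression plan does not define epigenetic changes as array methylation or limit them to the 24, and the article also plans a panel of 96 microRNAs. What stands is that the number is unexplained.

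**The aim is exploratory.** This is true, and it is why the point is an improvement to the design and not an error that invalidates the study.

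**Conclusion.** The point holds for the same-sample confirmation. The article itself fixes that discovery and confirmation use the same 24 samples, so this does not depend on detail left to an unseen plan. The step verifies the array reading. It does not show that a difference extends beyond those people, and it does not remove selection inflation.

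When the two assays agree at 0.7 to 0.9, it would pass about 67% to 99% of chance hits, against about 2.5% in independent samples. These shares rest on the assumed 12 v 12 split, threshold and agreement. They describe what happens to a chance hit, not how many of the declared hits are chance.

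The relation of the 24 to Table 2 and to the regressions is a matter for clarification. The detectable differences rest on an assumed split and assumed single-site levels and do not carry the conclusion.

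**What to change.** 1. Label the 24 arrays as the discovery set, and say that sequencing those samples is technical validation. Keep a few of them for that purpose.
2. Sequence the selected regions in about 24 other participants with banked blood or DNA. Test only those regions, require the same direction, and adjust for multiplicity over the regions tested. Report effect sizes from this second set.
3. State how many subjects are arrayed, at which visit or visits, how the 24 were chosen, and how they split between patients and controls. Then say in Table 2 and in Statistical analyses which methylation data, in which subjects, enter the regressions. If more than 24 samples are to be arrayed, correct the number.

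Cost: about the same number of sequencing assays, apart from the few kept for the technical check. The price is less cross-checking of array against sequencing, plus DNA preparation for the extra stored samples. The third item needs only a few sentences.
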